### Exploratory analysis

To explore the initial effect of the CM intervention, we will assess average level of patient activation, rates of guideline-concordant preventive primary care use, and physical- and mental-health-related quality of life. We will provide confidence intervals for these estimates.

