### Study aims

The specific aims of this study are as follows:

1. Use a collaborative intervention-planning framework to conduct intervention modifications.

2. Pretest intervention methods and materials with Hispanics with SMI and at risk for CVD.

3. Identify stakeholders' views of factors impacting the acceptability and sustainability of the modified intervention.

4. Pilot test the feasibility and acceptability of the modified intervention and initially explore its effect.

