### Phase IV

This phase will complete IM step 6 (evaluation) with a single group, pre-post, 12-month open pilot study (N = 30) carried out at WHCS. Two SW CMs will deliver the modified intervention, each carrying a caseload of 15 patients. Thirty adult Hispanic patients with SMI will be recruited. Inclusion and exclusion criteria are identical to those in phase IV. Based on the PCARE study recruitment rate of 69%, we will screen at least 45 patients to achieve our recruitment goal. A bilingual RA will recruit patients at WHCS through flyers, canvassing of waiting rooms, word of mouth, and provider referrals. We have allocated 18 months to this phase, which provides a six-month cushion for unanticipated problems with recruitment and attrition. Descriptions of the proposed measures for this study are presented in Table 3. As part of the planning process for this phase, the CAB will assess the appropriateness of these outcome measures for the intended patient population and, if necessary, identify other culturally relevant measures for key constructs (*e.g.*, acculturation, health literacy, illness perceptions).

**Table 3 T3:** Description of measures

Construct	Measure description
Feasibility	Study recruitment, assessment completion, and treatment attendance rates
Acceptability	CSQ and postintervention focus groups. The CSQ is an eight-item questionnaire scored on a four-point Likert-type scale. Scores range from 8 to 32, with higher score indicating higher satisfaction [68]. The CSQ is available in English and Spanish [69] and has excellent internal consistency in Hispanics [70].
Patient activation	PAM-13, [71] a 13-item scale that assesses patients' knowledge, skills, and confidence about self-management. Scores range from 0 (no activation) to 100 (high activation). PAM-13 has strong psychometric properties, including content and construct validity [71], has been tested across a range of chronic illnesses [72,73], and is available in English and Spanish.
Receipt of preventive primary care	PCARE study measure drawn from the USPSTF guidelines [74]. A total of 23 indicators are examined across four domains: (1) physical examinations, (2) screening tests, (3) vaccinations, and (4) education. Scored based on patients' medical records and self-report at baseline, three months, and six months. An aggregate preventive services score calculates the proportion of appropriate services obtained [18].

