Health and mental health-related quality of life	SF-12 [75], a self-report measure available in English and Spanish and validated among adults with SMI that generates two summary scores for physical and mental health-related quality of life [76]. Summary scores range from 0 to 100, with higher scores reflecting better health.
Covariates	Demographics: *e.g.*, race/ethnicity, age, gender, education, and marital status Acculturation: nativity, language dominance, time in the United States, age of migration; the Bidimensional Acculturation Scale [77], a 24-item self-report measure that uses separate four-point scales to tap acculturation-related changes in two languages. Barriers to medical care: a list of 11 common factors that may prevent patients from seeking medical care [78,79]. Comorbid medical conditions: a list of 17 common medical conditions by patient self-report.

CSQ = Client Satisfaction Questionnaire; PAM-13 = Patient Activation Measure; PCARE = primary care, access and referral; USPSTF = U.S. Preventive Services Task Force; SF-12 = Short Form Health Survey; SMI = serious mental illness.

The primary outcomes of the pilot study are feasibility and acceptability. Two post-intervention FGs will be conducted with study participants to explore their reactions to the intervention. Each FG will be composed of 8-10 patients and follow the FG methods described in phase II. Although this is not an efficacy trial, we would be remiss in not taking this opportunity to initially explore the intervention's effect, as measured by patient activation, receipt of preventive primary care, and physical- and mental-health-related quality of life. Covariates include demographics, acculturation, barriers to care, and comorbid medical conditions. The RA will assess patients at baseline, 6 months, and 12 months. Self-report measures and medical chart abstractions will be obtained. Patients will be asked for consent to access medical records at WHCS and their primary care clinic. The RA will conduct these abstractions under [name]'s supervision.

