### Primary analysis

To evaluate feasibility, we will estimate recruitment rate, assessment completion rate, and treatment attendance rate by sample proportions and provide their standard errors based on binomial distribution. We will evaluate acceptability by assessing patient satisfaction (CSQ scores) repeatedly over time (baseline, 6 months, and 12 months). We will analyze improvement in patient satisfaction by a linear mixed-effects model with random subject-specific intercepts to handle correlation between repeated measurements of the outcomes. We will include time as predictor of interest. Significance of improvement in satisfaction over time will be assessed by testing whether the slope of time is zero.

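### The exploratory analysis names levels and rates as its estimates, although in a single-group pre-post pilot the effect signal is change from baseline

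*Protocol article*

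**What the plan says.** The fourth study aim is to "Pilot test the feasibility and acceptability of the modified intervention and initially explore its effect". Phase IV describes a "single group, pre-post, 12-month open pilot study" with N = 30 and sets out to "initially explore the intervention's effect, as measured by patient activation, receipt of preventive primary care, and physical- and mental-health-related quality of life". On timing it states: "The RA will assess patients at baseline, 6 months, and 12 months".

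The only analysis text specific to these outcomes is the Exploratory analysis section. It says "we will assess average level of patient activation, rates of guideline-concordant preventive primary care use, and physical- and mental-health-related quality of life" and then "We will provide confidence intervals for these estimates". It names no change from baseline, no contrast between visits, no time term and no reference visit.

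The Primary analysis section, just before it, does specify change, but for the CSQ only: "We will analyze improvement in patient satisfaction by a linear mixed-effects model with random subject-specific intercepts", with time as the predictor and a test of its slope.

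Two other sections touch on repeated data. Preliminary analyses plans descriptive statistics by time point and graphs of patterns over time. Accounting for missing data in the analysis says in general terms that PROC MIXED accommodates continuous outcomes that are missing at some assessments.

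**The concern.** There is no control group, so the only quantitative signal of effect in the pilot is how patients differ from their own baseline. The estimates named for the effect outcomes are levels and rates. Someone following the text literally would model change in satisfaction and report levels, each with its own interval, for activation, preventive care and quality of life.

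Two things are then at stake. If patients are lost by 12 months, the baseline and 12-month means describe different sets of people, and their difference mixes change with selection. In addition, separate intervals around two means do not use the within-patient correlation, so they are not an interval for change. The pilot is meant to inform a larger trial, for which change and its variability are more useful than levels.

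**Working it through.** **Text comparison**

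| Section | Outcomes | Quantity named | Interval or test for change |
|---|---|---|---|
| Primary analysis | CSQ | improvement over time, mixed model | yes, slope of time |
| Exploratory analysis | activation, preventive care, quality of life | average level, rates | no |
| Preliminary analyses | variables relevant to the aims | descriptives and plots by time point | no |

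The mismatch between purpose and named estimate follows from this table and needs no arithmetic. The protocol states no precision figure, SD or within-patient correlation for the exploratory outcomes, so there is no planned figure to reproduce. What follows is illustration.

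**Inputs**
- N = 30 (Phase IV).
- 12-month assessment completion 0.69, the figure used in Precision analysis: 30 x 0.69 = 20.7, about 21 patients.
- Assumed: SD 15 on the 0-100 activation scale (PAM-13), equal at both visits.
- Assumed: correlation between baseline and 12 months of 0.3, 0.6 or 0.8.

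**Precision of change to 12 months, 95% margins**

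Paired, 21 pairs: 2.086 x 15 x sqrt(2(1 - rho)/21), where 2.086 is the t quantile on 20 degrees of freedom.
- rho = 0.3: 31.29 x sqrt(1.4/21) = 8.1
- rho = 0.6: 31.29 x sqrt(0.8/21) = 6.1
- rho = 0.8: 31.29 x sqrt(0.4/21) = 4.3

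Two means treated as separate, 30 and 21 patients: 1.96 x 15 x sqrt(1/30 + 1/21) = 8.4.

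The paired figures use the t quantile and the comparator uses 1.96. With 1.96 in both, the paired margins are 7.6, 5.7 and 4.1 (29.4 times the same square roots), and the pattern is the same. At rho = 0.2 the first formula gives 31.29 x sqrt(1.6/21) = 8.6, slightly worse than the comparator. The precision gain is therefore substantial at high correlation and absent at low correlation.

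**What separate level intervals would show**

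Baseline: 1.96 x 15/sqrt(30) = 5.4. Twelve months: 1.96 x 15/sqrt(21) = 6.4. Neither is an interval for change. A reader who judged by whether the two overlap would need a gap of about 5.4 + 6.4 = 11.8 points.

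**Possible dropout artefact**

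If the 31% lost score d points lower at baseline than those retained, whose mean is m, the baseline mean of all 30 is 0.69m + 0.31(m - d) = m - 0.31d. The 12-month mean then exceeds the baseline mean by 0.31d with no patient changing. That is 0 for d = 0, about 1.6 for d = 5 and 3.1 for d = 10. The protocol gives no value for d, and the sign could be the reverse.

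**The case against.** The strongest reply is that two sentences in a condensed article are being read as a decision. The section opens by stating that the purpose is to explore effect, the design is pre-post with three assessments, and descriptives by time point are planned. The natural reading is levels at each visit, compared over time, with the contrast left to an analysis plan. With complete data, the difference between visit means is exactly the mean within-patient change. The missing-data section also points to PROC MIXED, lets each available measurement contribute, and plans sensitivity analyses. It further treats the last scheduled assessment as end of treatment when no final one is obtained. If that means carrying the value forward, the set of patients does not change and the artefact above does not arise. Finally, the authors say that the pilot is not an efficacy trial.

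Much of this stands. A reader might infer that the pilot never estimates change, that levels carry no information on effect, or that dropout will produce apparent improvement. The documents support none of these. Levels at several visits do convey a crude change, the data for a proper estimate will be collected, and the comparison of 30 patients with 21 follows only if raw visit means are used, which the text neither states nor excludes.

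What does not fall is narrower. The section does not leave its estimate open: it names levels and rates and attaches the intervals to them. The missing-data section ties a multilevel model by name only to the CSQ, and its general remark on software defines no estimate of change for the other outcomes. The remark on the last scheduled assessment is ambiguous. Conceding that efficacy cannot be tested does not withdraw the aim of exploring effect.

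**Conclusion.** The point holds in this form: the exploratory estimates as named do not match the exploratory purpose, because no formal estimate of change with its own interval is stated for activation, preventive care or quality of life. This conclusion rests on the text alone.

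The size of the consequence is uncertain. The illustrative precision gain runs from almost none at correlation 0.3 to roughly half the margin at 0.8, under an assumed SD of 15 and 21 pairs. The dropout artefact depends on an unknown baseline gap and on how missing outcomes are handled. Feasibility and acceptability are the primary outcomes and are untouched, so the impact is moderate: worth correcting before analysis, but not a threat to the main conclusions.

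**What to change.** First reconcile the assessment times for preventive care. Table 3 scores it at baseline, three and six months, while the Phase IV text has assessments at baseline, 6 and 12 months. A 12-month change in that score cannot be defined until the two agree.

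Then restate the exploratory estimate as the mean within-patient change from baseline to 6 months and to 12 months, with 95% confidence intervals, for PAM-13, the preventive services score and both SF-12 summary scores. Obtain it from the random-intercept mixed model already planned for the CSQ, with visit entered as a category so that each change is estimated directly. The model uses all available assessments and the within-patient correlation, under the missing-at-random assumption that the protocol already makes. Keep the levels and rates at each visit as description.

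The cost is a few sentences of analysis text and the reconciliation of one table. No extra patients or new measures are needed; whether the preventive score needs another time point depends on how the schedule is reconciled.

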### Precision analysis

Since this is a pilot study for a future large randomized trial, we did not conduct a power analysis in accordance with recommendations in the new National Institutes of Health guidelines http://grants.nih.gov/grants/guide/pa-files/PAR-09-173.html and Kraemer and Kupfer [63]. Instead, we conducted precision analysis for the main study outcomes--feasibility and acceptability--by computing margin of error of an estimated rate to assess the precision that can be achieved by the proposed sample size. Margin of error is half the width of a confidence interval of an estimator. The smaller the margin of error, the tighter the confidence interval and the more precision we achieve for an estimator. We used the original PCARE [18] study treatment and completion assessment rates to estimate standard errors and margins of errors. PCARE's observed treatment completion rate was 0.68, with a sample size of 30, the standard error was 0.085 and the margin of error was 0.167. PCARE's observed assessment completion was 0.78 at 6 months and 0.69 at 12 months, the corresponding standard error is 0.076 and 0.084, respectively, and the margin of error is 0.15 and 0.17, respectively. For the CSQ scores (acceptability measure), when the standard deviation of the improvement of CSQ is 1, 2, or 4 points, the corresponding margin of error for estimating mean improvement is 0.18, 0.36, and 0.72, respectively. In all, our precision analysis indicates we have small margin of errors for each of our main study outcomes.

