### Quantitative analysis

All tests will be two-sided and performed at significance level α = 0.05.

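### The printed margins of error for mean CSQ improvement are about half of what the plan's own definition gives at n = 30

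*Protocol article*

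**What the plan says.** The pilot is described under Phase IV as a "single group, pre-post, 12-month open pilot study (N = 30"), and the same section makes feasibility and acceptability its primary outcomes. The CSQ score is the quantitative measure of acceptability.

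The Precision analysis section explains that no power analysis was done and that margins of error are given instead. It fixes the term: "Margin of error is half the width of a confidence interval of an estimator". The Quantitative analysis section sets the level: "All tests will be two-sided and performed at significance level α = 0.05".

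For treatment completion at a rate of 0.68, the section reports that "with a sample size of 30, the standard error was 0.085 and the margin of error was 0.167". It gives similar pairs for assessment completion at 6 and 12 months. For the CSQ it gives no standard error. It takes three illustrative SDs for the change in score (1, 2 and 4) and says only that "the corresponding margin of error for estimating mean improvement is 0.18, 0.36, and 0.72, respectively". The section ends: "In all, our precision analysis indicates we have small margin of errors for each of our main study outcomes".

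**The concern.** The paragraph uses one term, margin of error, for the rates and for the CSQ mean. A reader will assume that one rule lies behind both. For the rates, the margin is clearly larger than the standard error by the usual factor of 1.96. For the CSQ, the printed margin at SD 1 is 0.18, which is about the size of 1/√30, the standard error itself.

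At stake is what a reader believes the pilot can deliver on a primary outcome. The precision analysis stands in for a power calculation, and its closing sentence covers every main outcome. If the CSQ figures are too small by a factor of two, that sentence rests partly on wrong numbers. A reader planning the later, larger trial would also expect a CSQ estimate tighter than 30 patients can give.

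**Working it through.** **Inputs**

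- Definition of margin of error: half-width of a confidence interval (Precision analysis).
- Level: two-sided 0.05, hence a 95% interval and a normal quantile of 1.96 (Quantitative analysis).
- n = 30 (Phase IV and Precision analysis).
- SD of CSQ improvement: 1, 2 and 4 points (Precision analysis).
- Rates: 0.68, 0.78 and 0.69 (Precision analysis).

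**Step 1: reproduce the rate margins.** SE = √(p(1 − p)/30) and margin = 1.96 × SE.

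| Rate | SE | Margin | Printed SE, margin |
|---|---|---|---|
| 0.68 | 0.0852 | 0.1669 | 0.085, 0.167 |
| 0.78 | 0.0756 | 0.1482 | 0.076, 0.15 |
| 0.69 | 0.0844 | 0.1655 | 0.084, 0.17 |

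All three reproduce. This confirms the 95% level, the normal quantile and n = 30 from the paragraph's own figures.

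**Step 2: apply the same rule to the CSQ.** SE = SD/√30 and margin = 1.96 × SE. The t-based version uses the 0.975 quantile on 29 degrees of freedom, 2.045.

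| SD | SE | Margin (normal) | Margin (t) | Printed |
|---|---|---|---|---|
| 1 | 0.183 | 0.358 | 0.373 | 0.18 |
| 2 | 0.365 | 0.716 | 0.747 | 0.36 |
| 4 | 0.730 | 1.431 | 1.494 | 0.72 |

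The ratio of recomputed to printed is 1.99 with the normal quantile and 2.07 with t.

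**Step 3: look for a reading that yields the printed figures.**

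- Another confidence level: 90% gives 0.30, 0.60 and 1.20; 80% gives 0.23, 0.47 and 0.94. Neither matches. Taken as half-widths at n = 30, the printed values correspond to an interval of about 68%.
- Another n: a 95% margin of 0.18 at SD 1 needs (1.96/0.18)² = 118.6, about 119 patients.
- The bare standard error: 0.18, 0.37 and 0.73. Close, but two of the three differ in the second decimal.
- Half of the correct margin: 0.179, 0.358 and 0.716. All three match after rounding.
- The slope per visit in a random-intercept model, visits coded 0, 1, 2: if the SD of a change between two visits is SD, the residual SD is SD/√2. The squared deviations of the visit codes sum to 2, so the slope has SE = (SD/√2)/√(2 × 30) = SD/(2√30). Its 95% margin is 0.179, 0.358 and 0.716. All three match here too, and the 12-month improvement is two slopes, so its margin returns to 0.358, 0.716 and 1.431.

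**The case against.** The strongest defence is the slope reading. The Primary analysis section does analyse CSQ improvement as the slope of time in a random-intercept model over three visits, and the margin for a slope per visit fits all three printed values. Under that model the SD of change is the same over 6 or 12 months, so the SD and the mean could both refer to one visit interval. On this view the arithmetic is right and only the unit is unlabelled. What stands is that the origin of the figures is unknown. The defence does not rescue the text, which gives a margin for mean improvement from the SD of improvement and mentions neither a slope nor a visit interval. The margin for the 12-month improvement would still be twice the printed one.

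The defence is also right about consequence. The SDs are hypothetical, and no progression rule uses the margins. The section assesses the precision of a sample size already proposed, and Phase IV describes two care managers with 15 patients each. Acceptability is also examined in focus groups after the intervention.

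A reader might be tempted to go further in four ways that the article does not support:

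- **That the half-width was halved a second time.** The numbers fit, but so does the slope margin, and the standard error is close.
- **That the true margins are about 2.5 times those printed because only 69% will be assessed at 12 months.** The statement "PCARE's observed assessment completion was 0.78 at 6 months and 0.69 at 12 months" reports the earlier study and is used to show the precision of a rate; it is not a forecast for this pilot. Treating 0.69 × 30 ≈ 21 as the analysed n gives t-based margins of 0.46, 0.91 and 1.82, but only for a complete-case analysis. The missing-data section specifies a mixed model that uses every available measurement.
- **That ±17 percentage points cannot be called small.** That margin is correctly computed and openly printed, and the article sets no threshold. Even the corrected 1.43 points is about 6% of the CSQ's 24-point range (8 to 32), so the correction alone does not show the word to be false for the CSQ.
- **That these margins are the only justification for 30 patients.** The caseload described in Phase IV and the focus groups speak against this.

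**Conclusion.** The point holds as an error in stated precision. Under the article's definition, and by the rule that reproduces its own rate margins, the 95% margins for mean CSQ improvement with 30 patients are 0.36, 0.72 and 1.43, not 0.18, 0.36 and 0.72. The overstatement is about two-fold: 1.99 by the plan's normal approximation and 2.07 with t.

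This rests on three things: a 95% interval, 30 patients measured, and the plain meaning of mean improvement as the average of the change whose SD is given. The first two are confirmed by the rate figures. If a slope per visit was meant, the fault is an unnamed quantity rather than a miscalculation, but the sentence still misleads about the 12-month improvement by the same factor.

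Dropout will widen the margins. By how much cannot be fixed from the article, since it depends on this pilot's own completion and on the within-patient correlation. The effect is on what the article claims about a primary outcome. The sample size, the planned tests and the conduct of the pilot are unaffected.

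**What to change.** In the Precision analysis section:

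1. Replace the three CSQ margins with 0.36, 0.72 and 1.43 for mean improvement at n = 30 (or 0.37, 0.75 and 1.49 if t quantiles are preferred, saying so). Printing the standard errors alongside (0.18, 0.37 and 0.73) would match the way the rates are reported.
2. If the printed values were meant for another quantity, such as the slope per visit, name it with its time unit and add the margin for the 12-month improvement.
3. Add that the figures assume all 30 patients are measured and will be wider with dropout.
4. Base the closing sentence on the corrected figures.

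N stays at 30 and no analysis changes. The change is to wording and three numbers, and the only cost is a less favourable stated precision.
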